## Abstract

**Background:**

Recent projections suggest that by the year 2030 depression will be the primary cause of disease burden among developed countries. Delivery of accessible consumer-focused evidenced-based services may be an important element in reducing this burden. Many consumers report a preference for self-help modes of delivery. The Internet offers a promising modality for delivering such services and there is now evidence that automated professionally developed self-help psychological interventions can be effective. By contrast, despite their popularity, there is little evidence as to the effectiveness of Internet support groups which provide peer-to-peer mutual support.

**Methods/Design:**

Members of the community with elevated psychological distress were randomised to receive one of the following: (1) Internet Support Group (ISG) intervention, (2) a multi-module automated psychoeducational and skills Internet Training Program (ITP), (3) a combination of the ISG and ITP, or (4) an Internet Attention Control website (IAC) comprising health and wellbeing information and question and answer modules. Each intervention was 12 weeks long. Assessments were conducted at baseline, post-intervention, 6 and 12 months to examine depressive symptoms, social support, self-esteem, quality of life, depression literacy, stigma and help-seeking for depression. Participants were recruited through a screening postal survey sent to 70,000 Australians aged 18 to 65 years randomly selected from four rural and four metropolitan regions in Australia.

**Discussion:**

To our knowledge this study is the first randomised controlled trial of the effectiveness of a depression ISG.

**Trial registration:**

Current Controlled Trials ISRCTN65657330.

## Background

It has been projected that depression will be the leading cause of disease burden in 2030 [1]. Lifetime prevalence of depression is high [2] and depressive episodes are frequently persistent and recurrent [3]. Moreover, only a minority of people with depression receive evidence-based treatment [4].

It is likely that the undertreatment of depression is due in part to lack of availability and accessibility of services [5], an unwillingness to seek help due to the stigma associated with depression [6] and a preference among some people with depression for employing self help methods for coping with the condition. One potential means for increasing treatment coverage and reducing burden is to facilitate the large scale dissemination of self help methods which reduce the need for the health workforce involvement and circumvent the stigma associated with seeking face-to-face help.

There is some evidence that self help interventions delivered online can be effective in reducing depressive symptoms [7]. In particular, a number of studies have reported a reduction in depressive symptoms associated with the use of automated online programs in the absence of clinical input (e.g., [8-14]). Online programs have also been demonstrated to reduce the stigma associated with depression [15,16] and to increase mental health literacy among people with elevated depressive symptoms [8,17]. Less is known about the effect of these programs on other factors such as empowerment, quality of life, self esteem, disability, and service use. Further, although a frequently cited advantage of online psychological applications is their potential for use with under-served rural populations [18] there have been no direct comparative studies of the acceptability and effectiveness of these programs in rural compared to metropolitan regions [7].

Research into the effectiveness of online interventions for depression has been focused primarily on applications designed to deliver psychological skills training. However, the widespread availability of the Internet has stimulated the development of a large number of online 'mutual support' or 'self help support' groups. Such support groups have been estimated by Eysenbach to be used by 'millions' of consumers daily [18] and there is evidence that they are particularly popular among consumers with depression [19]. However, the efficacy of such Internet support groups (ISGs) has not been established.

A recent systematic review of depression ISGs identified no randomised controlled trials of the effectiveness of the groups, for individuals with depression, in reducing depressive symptoms or in improving other psychological, mental health, service-related or other outcomes [20]. However, there was some evidence that peer-to-peer support groups might be associated with a reduction in depressive symptoms. In particular, in a prospective cohort study, Houston [21] reported a reduction over 6 months in depressive symptoms among high frequency users of public internet support groups after controlling for initial severity of symptoms. In addition, a systematic review of efficacy trials of ISGs for consumers with a range of health conditions yielded some encouraging evidence that such ISGs may be effective in reducing depressive symptoms among women with breast cancer [22].

It is possible however, that the primary effect of depression support groups is on outcomes other than symptomatology. For example, it is often claimed that support groups increase consumer empowerment and social support [23,24]. However, to date there have been no quantitative studies of the effect of depression ISGs on outcomes such as empowerment, self esteem, social support, quality of life or other factors such as depression knowledge and help seeking.

One potential limitation of fully automated online programs is the likelihood of substantial dropout during their unguided use [25]. Automated messages and reminders might reduce attrition rates in such circumstances [26]. It has also possible that participation in an ISG might facilitate adherence to online applications. Indeed, many online chronic disease management programs employ ISGs (e.g., see [20]). However, to our knowledge, to date there have been no systematic studies of the effect of online peer-to-peer support groups on adherence or outcomes among consumers receiving internet applications.

A final limitation of available research is that the majority of randomised controlled studies of e-mental health programs have employed wait list control groups [27]. A small number of studies have employed an attention control group or a psychoeducational controls. However, these studies have some limitations. For example, Christensen and her collaborators used a telephone attention control but the control group did not receive an internet intervention [8,9,15]. Some studies have used an online psychoeducational website as a control (e.g., [28-30]). However, a recent meta-analysis demonstrated that the provision of mental health information may reduce depressive symptoms among adults with depression or depressive symptoms [31]. To date no study of the efficacy of e-mental health intervention has employed an attention control condition which both comprised a website and contained plausible content not containing depressive or anxiety psychoeducational information.

### Objectives of the ANU WellBeing study

The primary objectives of the study are to (i) evaluate the efficacy of a depression Internet Support Group (ISG) and an automated psychoeducational and skills Internet Training Program (ITP) for reducing depressive symptoms relative to a plausible Internet Attention Control condition (IAC); to evaluate the relative efficacy of the ITP, ISG and combined ITP and ISG interventions; and (iii) to ascertain if the adherence rates and magnitude of improvement in depressive symptoms is greater for the ISG and ITP interventions combined than for either condition alone.

Secondary objectives of the study are to (i) evaluate the effect of the two experimental interventions on anxiety, disability, social support, loneliness, self-esteem, empowerment, loneliness, depression literacy, stigma and help seeking in people with elevated depressive sympotms; and (ii) to compare the outcomes of these interventions in rural and metropolitan residents.

## Methods/Design

### Trial Design

Members of the community with elevated levels of depressive symptoms were randomised in a 2 by 2 quasi-factorial design to receive either the ISG, the ITP, a combination of the ISG and IPT or a plausible internet-based attention control (IAC) (see Table 1). Measures were administered at screening, baseline, post-test, and 6 and 12 months after the intervention commencement.

**Table 1 T1:** Quasi-factorial trial design and target sample sizes per cell.

	Internet support group (ISG)		
**Automated skills training program (ITP)**	**No ISG**	**ISG**	**Target total**

**No ITP**	125 (IAC)	125	250

**ITP**	125	125	250

Target total	250	250	500

Approval to conduct the trial was granted by The Australian National University Human Research Ethics Committee (Protocol 2007/2259). The study protocol is registered with the Controlled Clinical Trials registry (ISRCTN65657330).

### Participant recruitment

Participants in the ANU WellBeing Study have been recruited via postal invitation and survey of 70,000 adults aged between 18 to 65 years who were randomly selected from the electoral rolls of four rural and four metropolitan Australian electoral divisions. Registration on the electoral roll is compulsory for all Australian citizens. Participants were selected from the division list using the 'select cases' random selection facility in SPSS. The metropolitan samples comprised registrants from one electoral division in Canberra, The Australian Capital Territory; two electoral divisions in Melbourne, Victoria (Maribyrnong, Higgins); and one division in Sydney, NSW (Bennelong). The rural divisions were located in Victoria (Indi, Murray) and New South Wales (Hume, Riverina). Divisions were selected from those which had a moderate (51%) to high proportion (>62.2%) of households with internet access [32]. Participants were oversampled in the rural divisions to adjust for lower internet usage in these regions.

The screening survey was accompanied by a letter and brochure which described both an enclosed 'WellBeing' screening survey and an intervention project ("The Wellbeing Promotion Study"). The participant was informed that the WellBeing survey was designed to 'find out more about the mental health of Australians in the city as well as in rural areas' and that the WellBeing Promotion Study was designed to 'look at the usefulness of self help internet programs for improving emotional well being and preventing or reducing the symptoms of depression'.

Survey respondents who met the eligibility criteria for the WellBeing study (see Table 2), including elevated levels of psychological distress as measured by the Kessler Psychological Distress (K10) scale, and a willingness to be contacted about participating in the trial were notified by letter that they would telephoned by a project interviewer to discuss the project. The assigned interviewer subsequently contacted the eligible respondent to provide further details about the trial including a brief description of the four conditions to which they might be randomly allocated, to provide information about the participant time commitment involved, to answer questions about the study, and to confirm that the respondent satisfied the inclusion criteria for the study.

**Table 2 T2:** Inclusion and exclusion criteria for the WellBeing trial

Inclusion	Exclusion
Age 18 to 65 years	Self-reported current or imminent treatment from a mental health professional or mutual support group at the time of recruitment.

Kessler Psychological distress (K10) score > 22	Current treatment with Cognitive Behaviour Therapy.

Home or work access to the Internet	Self-reported current or past experience with or diagnosis of psychosis, schizophrenia or bipolar disorder.

Consent to participate	Current or prior participation in another project conducted by the lead investigator's research centre.

Eligible individuals who agreed on the telephone to participate in the project were randomised (see below) to one of the four trial conditions and were sent an information sheet about the project and the intervention conditions together with a consent form. At this point, however, neither they, their interviewer nor the project coordinator were informed of their randomisation status. Randomisation prior to consent and completion of the pre-intervention was undertaken for pragmatic reasons as the trial required the participants in the internet support groups to commence simultaneously. Undertaking stratified randomisation post-consent and post-baseline survey would have either introduced a significant delay between screening and baseline measures and the commencement of the intervention or reduced the available pool of participants.

Those participants who returned consent forms were sent a letter informing them of the condition to which they had been randomised together with a 14 or 15 page user guide containing a week by week overview of their intervention, a 'Frequently Asked Questions' section and a 'Technical Tips' page.

Recruitment to the WellBeing Study was conducted in three waves (Pilot, Wave 1, Wave 2) between August 2008 and May 2009. A subsample of 7000 surveys (randomly selected from the two metropolitan divisions of Canberra and Maribyrnong and the two rural divisions of Murray and Indi) were employed to pilot the survey and protocol. After the successful completion of the intervention phase of the pilot, a further 28,000 surveys were sent to residents in the above divisions. Since these screening surveys did not yield the target sample size for the study, a further 35,000 surveys were sent to the divisions of Bennelong, Higgins, Murray and Riverina.

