### Intervention Study Procedure

All participants who provided written consent were sent a user ID and password by automated email. A second automated email sent one week prior to the commencement of the intervention directed them to log onto the website to complete the online baseline survey.

Each of the four conditions was then delivered over a period of 12 weeks. Participants received a weekly automated email informing them when the next module of their program was available. Those who failed to log onto the module were sent an email reminder four days after the initial email. Those who failed to log in thereafter received a telephone reminder from their interviewer. The current week's module was only available after first completing the modules assigned in the preceding week or weeks.

At the end of the 12-week trial, an automatic email was sent to participants requesting that they complete the post-intervention survey. Reminders were sent according to the protocol employed at baseline. Further follow up using this protocol was undertaken at 6 months and 12 months after the commencement of the intervention. The flow of participants is shown in Figure 4.

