### Measures

Table 4 provides a summary of measures taken at each assessment point.

**Table 4 T4:** Measures employed in the screening and baseline, post intervention and follow-up phases of the WellBeing Study

	Screening	Baseline	Post-test	6 month	12 month
Depressive symptoms (CES-D)		X	X	X	X

Anxiety symptoms (PSWQ)		X	X	X	X

Quality of Life		X	X	X	X

Disability		X	X	X	X

Self-esteem		X	X	X	X

Perceived social support		X	X	X	X

Loneliness		X	X	X	X

Depression knowledge		X	X	X	X

Stigma	X	X	X	X	X

Help-seeking behaviours		X	X	X	X

Empowerment		X	X	X	X

User perceived utility of the Internet		X	X	X	X

Satisfaction & user perceived benefits/negative effects of intervention			X	X	X

Participation in healthcare			X		

Sociodemographics	X				

Psychological distress (K10)	X				

User perceived mental health status	X				

Depression & general anxiety symptoms (DASS-21)	X				

Social anxiety screening (BSPS)	X				

Panic screening	X				

Information needs	X				

Intervention group preference	X				

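### The first CES-D score appears to be taken after participants learn their condition, so any reaction to allocation can bias the planned change-from-baseline contrasts

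*Protocol article*

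**What the plan says.** The order of events has to be assembled from several sections of the protocol article.

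- **Randomisation** (Participant recruitment): "Eligible individuals who agreed on the telephone to participate in the project were randomised (see below) to one of the four trial conditions". The same section acknowledges the early timing: "Randomisation prior to consent and completion of the pre-intervention was undertaken for pragmatic reasons". The reason given is that internet support group (ISG) members had to start together.
- **Concealment** (same section) is stated for the mailing of the information sheet and consent form: "At this point, however, neither they, their interviewer nor the project coordinator were informed of their randomisation status".
- **Disclosure** (same section) follows return of consent: "Those participants who returned consent forms were sent a letter informing them of the condition to which they had been randomised". A 14 or 15 page guide with a weekly overview of the intervention was enclosed.
- **Baseline survey** (Intervention Study Procedure): consenters received login details, and then a second email, one week before the start, "directed them to log onto the website to complete the online baseline survey".
- **Measures** (Table 4): the CES-D row has marks at baseline, post-test, 6 and 12 months and none at screening. The K10 and the row "Depression & general anxiety symptoms (DASS-21") are marked at screening only.
- **Analysis** (Planned data analysis and sample size): a priori contrasts within a condition-by-time MMRM, with the detectable effect of about 0.25 SD expressed as change from baseline.

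**The concern.** A baseline should not be open to influence by the allocation. Here the letter is tied to return of consent and the survey to a later email, and nothing says that the letter was held until the survey was submitted. The need for a simultaneous start explains why allocation was generated early. It does not explain why participants were told early.

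A reaction is plausible. Interviewers had described all four conditions beforehand, the screening survey asked which group people preferred, the weekly contents differ sharply (Table 3), and the CES-D is self-report. If people who drew the attention control (IAC) felt worse when they completed the baseline, or those who drew an active programme felt better, mean baseline CES-D would differ by arm for a reason other than chance. A change-from-baseline contrast would then carry that difference into the primary result. Disclosure before the survey also leaves room for baseline completion to differ by arm.

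**Working it through.** **Inputs from the article:** 500 randomised, 125 per arm (250 per margin of the 2 by 2 layout); power 80%; pre-post correlation r = 0.5; detectable effect about 0.25 SD. **Assumptions:** two-sided alpha 0.05 (not stated), and a baseline shift d of 0.05 to 0.20 SD between arms (no size is given).

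**1. The article's own figure.** SD of change = √(2(1 − r)) = √(2 × 0.5) = 1.0. Detectable effect = (1.960 + 0.842) × 1.0 × √(2/250) = 0.2506 SD, so 0.25 SD reproduces for 250 v 250. For one arm against another it is 2.802 × √(2/125) = 0.354 SD. Both sizes are carried below; the bias itself does not depend on n.

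**2. How a shift enters each analysis.** Let Δ be the true benefit over control at follow-up. Let the reaction raise the control-minus-active difference in baseline CES-D by d, with a fraction p of it still present at follow-up.

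- Change score: Δ + pd − d = Δ − (1 − p)d
- ANCOVA on the online baseline: Δ + pd − rd
- Post-baseline model not using the online baseline: Δ + pd

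If the reaction has gone (p = 0), the biases are −d, −0.5d and 0. If it persists fully (p = 1), they are 0, +0.5d and +d.

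**3. Size for a transient shift (p = 0).** SE of the change contrast = √(2/125) = 0.1265 or √(2/250) = 0.0894. With no true effect, the two-sided error is Φ(−1.96 + d/SE) + Φ(−1.96 − d/SE).

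| d (SD) | Change-score bias as share of 0.25 | ANCOVA bias (SD) | Change-score error, 125 v 125 | Change-score error, 250 v 250 |
|---|---|---|---|---|
| 0.05 | 20% | 0.025 | 6.8% | 8.6% |
| 0.10 | 40% | 0.050 | 12.4% | 20.1% |
| 0.15 | 60% | 0.075 | 22.0% | 38.9% |
| 0.20 | 80% | 0.100 | 35.3% | 60.9% |

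**4. Direction.** At d = 0.10 and 125 v 125, d/SE = 0.79. The two tails are Φ(−1.17) = 12.1%, in control's favour, and Φ(−2.75) = 0.3%, in the intervention's favour, against 2.5% each with no shift. If the true effect is 0.25 SD, the expected change contrast falls to 0.15 SD. Power falls from 79.8% to 38.9% (250 v 250) or from 50.7% to 21.9% (125 v 125).

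**5. Precision of the alternative.** At r = 0.5 the change score has SD 1.0, the same as an unadjusted follow-up score. Not subtracting the baseline therefore costs nothing against a change contrast, and any correlation R between the screening scores and follow-up CES-D gains precision: residual SD √(1 − R²). ANCOVA on the online baseline has residual SD √(1 − 0.25) = 0.866, so the alternative is less precise than that only if R is below 0.5.

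**The case against.** Several points on the other side are sound.

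- **The sequence is inferred.** No sentence says that the letter came before the survey. This is true, but it is the natural reading and nothing contradicts it.
- **The size is assumed.** The control was built to be plausible, its weekly questions are introduced as bearing on mood, and nothing shows that participants saw it as a poor draw. The shift could be zero, and then there is no bias. This stands.
- **Direction.** A reader might infer that the flaw could manufacture efficacy. Disappointment in control and hope in the active arms, if transient, push the other way, as step 4 shows.
- **Persistence.** A reader might infer that any shift passes in full into the change score, and that a post-baseline model is free of bias. The first is true only if the reaction has gone by follow-up. Whatever persists cancels in the change score but stays in the post-baseline model, in the intervention's favour. Neither model is safe in every case.
- **Analysis set.** A reader might infer that people without a baseline survey are dropped. The article states intention to treat and MMRM and defines no set that requires a baseline. Differential completion is something to report, not an established fault.
- **Logistics.** Holding the letter and guide would have compressed their delivery into the last week, or required an earlier survey. That is a fair practical point, but the article does not offer it as a reason for early disclosure.
- **Timing.** The pilot and wave 1 have finished 12-month follow-up and wave 2 has finished 6 months. Replacing the primary analysis now would carry its own risk, which argues for adding a model rather than substituting one.

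**Conclusion.** The point holds as a design limitation of unknown size. Baseline CES-D is, on the natural reading of the article, a post-randomisation, unmasked self-report, and the planned contrasts rest on it. A transient shift of 0.05 to 0.20 SD would bias a change contrast by 20% to 80% of the 0.25 SD target, and ANCOVA by half that. These figures rest on the assumed shift, r = 0.5 and, for the error rates and power, a two-sided alpha of 0.05.

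Against IAC the likely harm is masked benefit and lost power. Between active arms the direction cannot be stated. The documents do not support a conclusion that the trial is biased towards efficacy, or that the planned model must be discarded. They do support the conclusion that the planned model alone cannot show whether its baseline was affected.

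**What to change.** Before analysis, prespecify alongside the planned model:

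1. An MMRM of CES-D at post-test, 6 and 12 months on condition by time, adjusted for screening K10 and DASS-21 depression. It neither subtracts nor conditions on the online baseline.
2. Inclusion of everyone who returned consent, in the arm assigned, whether or not they completed the baseline survey. As described, consent was returned before disclosure, so this set remains comparable across arms.
3. Reporting of baseline completion and mean baseline CES-D by arm.
4. A stated rule that the efficacy conclusion is qualified if the two models disagree. Because they respond in opposite ways to a persisting reaction, disagreement is informative.

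The cost is a little more analysis on data already collected. Some precision is lost relative to ANCOVA on the online baseline if the screening scores predict CES-D less well than that baseline does. The design remedy is to hold the allocation letter and guide until the baseline survey is submitted. Recruitment ended in May 2009 and no further wave is described, so that remedy applies only to a future trial.
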